**Figure 2. F2:**
[figure not shown]
Sickle cell disease community health worker intervention flowchart.

### Procedures and Data Collection

The primary outcomes for this study are patient satisfaction and self-care behaviors (including appointment keeping, tracking health issues, and managing medications). These will be assessed using validated instruments at baseline and after intervention (following the 6-month CHW-integrated PCCC model). Feasibility will be assessed through (1) enrollment numbers within a 2-year time frame, (2) retention, (3) intervention completion, and (4) acceptability of the intervention among participants.

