### Study Design, Setting, and Sample

This study will use a pre-post, nonrandomized, 6-month longitudinal intervention design, implemented using questionnaires and semistructured interviews (Figure 2). Enrollment will occur through the Augusta University Sickle Cell Center’s satellite clinic, Phoebe Putney Cancer Center, in Albany, Georgia. This site has not previously worked with a CHW, either directly or through a community-based organization.

Eligible participants will be adults with SCD aged 18‐45 years. Given the target sample size (n=40), at 80% power and α=.05, we can detect small to moderate effect sizes (*r*^2^=0.4 to 0.6) using a 2-tailed paired *t* test [22]. This sample includes an expected 20% attrition rate. There are currently 97 eligible individuals seeking SCD care at this location. This is more than double the expected enrollment of 30 participants. Using a rolling recruitment process, the PI will work with MTS to enroll additional participants if an enrolled participant is lost to follow-up. The assumption of a small to moderate effect is conservative, given that studies designed to improve self-care in SCD report a medium effect size (*d*=0.71) [8,23].

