### Study Procedures

Adults with SCD (aged 18‐45 years) will be recruited from the Augusta University Sickle Cell Center’s satellite clinic in Albany, Georgia. Clinic staff will identify participants who meet the inclusion criteria. For eligible patients, clinic staff will describe the study and offer participation during the patient’s regularly scheduled clinic visit. During the visit, interested patients will provide written informed consent and the link to the baseline questionnaire to be completed via Qualtrics. Each participant will receive a $20 gift card after completing the questionnaires. Following enrollment, participants will be referred to MTS for assignment to a CHW.

The CHW will schedule an initial session (60 minutes) with participants, followed by 5 subsequent monthly sessions (virtual or telephone-based) scheduled for 30 to 60 minutes, for a maximum of 6 patient contact hours over 6 consecutive months. During each monthly session, the CHW will educate participants on SCD management (ie, preventive services, management of acute complications, and management of chronic complications). The CHW will use a subjective, objective, assessment, and plan (SOAP) format for reporting via Qualtrics. The SOAP form is a standardized documentation method used by health care providers to systematically record patient information, thereby enhancing communication about health care experiences [24]. By organizing patient encounters into 4 distinct sections, the SOAP note serves as a clear framework for evaluating patient data and outlining management strategies [24]. This report will allow the CHW to document observations from patient interactions.

After completion of the sixth and final session, the CHW will provide a link to the postintervention questionnaire to be completed via Qualtrics. The postintervention questionnaire contains a question of interest about participating in debriefing interviews. We will conduct semistructured debriefing interviews with patients (n=35 approximately) to determine the perceived feasibility and acceptability of the study procedures. A member of the research team will conduct the interviews using a semistructured interview guide. Interviews are expected to last 45 to 60 minutes, and compensation will be a US $25 gift card. All incentives will be distributed by the PI per the institutional review board–approved protocol for research involving human subjects.

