## Results

Quantitative and qualitative results will be triangulated. The qualitative debriefing interviews will allow us to expand on implementation and practical challenges. We will also identify areas for improvement regarding the intervention logistics and patient recommendations in preparation for a larger study. A challenge of this novel approach is the limited precedent for integrating a CHW to supplement SCD specialty care. However, this study is expected to yield important preliminary data for developing an optimally effective intervention to be tested in a future feasibility study. As of March 2026, we have enrolled 16 participants.

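### Enrolment feasibility is a head count, which cannot separate few patients being offered the study from many declining it, and which rises when losses are replaced

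*Protocol article*

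**What the plan says.** Under Procedures and Data Collection the protocol article states: "Feasibility will be assessed through (1) enrollment numbers within a 2-year time frame". The other three feasibility measures are retention, completion of the intervention, and acceptability among participants.

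Under Study Design, Setting, and Sample it adds: "There are currently 97 eligible individuals seeking SCD care at this location". The only use made of this figure is to argue that the pool is large enough: "This is more than double the expected enrollment of 30 participants". The same section gives the target: "Given the target sample size (n=40), at 80% power and α=.05". It also provides for rolling recruitment, with further participants enrolled when one is lost.

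Under Study Procedures, "Clinic staff will identify participants who meet the inclusion criteria"; staff then make the offer at a scheduled clinic visit, and interested patients consent. The article describes no count of patients approached or declining, and Data Analysis plans no uptake proportion. The Results section says that areas for improvement will be identified "in preparation for a larger study".

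**The concern.** Feasibility is the first specific aim, and enrolment is the first measure listed for it. Recruitment can fall short for two reasons: eligible patients are not offered the study, or they are offered it and decline. The remedies differ. The first calls for more contact by staff, the second for a change in the offer or the intervention. A count takes the same value in both cases.

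The count also mixes enrolment with attrition. If each lost participant is replaced, a study that keeps its participants badly enrols more people in total, so poor retention would look like good enrolment.

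A larger study needs acceptance per approached patient and reach per eligible patient to set its number of sites and its recruitment period. The other feasibility measures do not supply these. Acceptability is judged among participants, and the interviews cover enrolled patients, CHWs and clinic staff, so no patient who declined is heard.

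**Working it through.** **Inputs.** From the article: 97 currently eligible; target 40; expected enrolment 30; 20% expected attrition; 16 enrolled as of March 2026. Not given: the number approached. I assume a range from 20 or 40 up to all 97.

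**The article's own comparison.** 97/30 = 3.23, so the statement that the pool is more than twice the expected enrolment is true. It also holds for the target: 97/40 = 2.43. (That the section gives both 30 and 40 is a separate matter, to be reconciled before any count can be judged against a goal.)

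**Crude share of the eligible snapshot**, enrolled/97, with Wilson 95% intervals:
- 16/97 = 16.5% (10.4% to 25.1%)
- 30/97 = 30.9% (22.6% to 40.7%)
- 40/97 = 41.2% (32.0% to 51.2%)

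The intervals are illustrative. The 97 is the site's stated pool at one time, not a random sample, and 16 is an interim number.

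**Uptake among those approached**, enrolled/approached (numbers approached assumed):

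| Enrolled | 20 approached | 40 approached | 60 approached | 97 approached |
|---|---|---|---|---|
| 16 | 80% | 40.0% | 26.7% | 16.5% |
| 30 | – | 75.0% | 50.0% | 30.9% |
| 40 | – | 100% | 66.7% | 41.2% |

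Within each row the stated measure takes one value, while acceptance varies by a factor of about 2.4 (rows 30 and 40) to 4.8 (row 16).

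**Effect of replacement.** If 40 enrol, 20% are lost and each is replaced once, the count becomes 40 + 0.20 × 40 = 48. With no loss it stays at 40. This ignores losses among the replacements. It also sits uneasily with the statement "This sample includes an expected 20% attrition rate", which suggests that the 40 already allows for loss; the article does not say how the two provisions combine.

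**The case against.** The strongest reply is that this is an omission from a condensed article. The measure appears in a one-sentence list, none of the four measures has a formula, and a screening log may exist in the full protocol. That log cannot be ruled out, and its absence from the article is not the point. The article does name the enrolment measure, and the measure named is a count; if a log exists, the fix is to make it the stated measure.

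A second reply is that Study Procedures has staff offer the study to eligible patients at their visits, so the number approached may be close to the number who attend. This narrows the plausible range if the procedure is followed fully, but nothing described would confirm it. Interviews with clinic staff may bring recruitment problems to light, though without numbers and without patients who declined.

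Some stronger readings are tempting and are not supported:
- A reader might infer that nothing can be said about uptake in the eligible population. The 97 does allow a crude share.
- A reader might infer that enrolment closes at the target, so that the count shows only whether the target was met. The article gives a target and a replacement provision, but no closing rule.
- A reader might fault the plan for not showing how representative the enrollees are. That is not one of its stated aims.

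**Conclusion.** The point holds for the form of the first feasibility measure. As written, it cannot separate patients never offered the study from patients who declined, and it increases with replacement of losses. Over the assumed 40 to 97 approached, a final count of 40 fits acceptance of 41% to 100%, and a count of 30 fits 31% to 75%. The eligible pool gives only a share of a single snapshot (16.5% at 16 enrolled, 41% at 40) for a recruitment period of 2 years.

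The ranges rest on assumed numbers approached; the shares of 97 rest on the article's figures alone. No primary outcome, test or stated calculation depends on the measure, and enrolment is one of four feasibility components. It is a cheap improvement, worth making because the study is meant to inform a larger one.

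**What to change.** Under Procedures and Data Collection, define enrolment feasibility as the numbers eligible, approached and consented over the 2-year window. Report consented/approached and consented/eligible, each with a 95% confidence interval. Exclude participants enrolled as replacements or report them separately. Record the main reason for refusal where a patient volunteers it. Keep the head count as a descriptor.

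The clinic staff who already identify patients and make the offer should keep the tally prospectively from now on. At the March 2026 figure, 40 − 16 = 24 of the target were still to be enrolled, so prospective capture could cover most of it. For patients already enrolled, report only the eligible denominator: clinic schedules show who attended, not who was approached or who declined.

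Aggregate age and sex of non-enrollees would be useful but is optional and subject to IRB approval. The article describes approval for surveys and interviews, and these data would come from people who did not consent.

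The cost is a little staff time and a possibly less favourable enrolment figure.

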### Study Procedures

Adults with SCD (aged 18‐45 years) will be recruited from the Augusta University Sickle Cell Center’s satellite clinic in Albany, Georgia. Clinic staff will identify participants who meet the inclusion criteria. For eligible patients, clinic staff will describe the study and offer participation during the patient’s regularly scheduled clinic visit. During the visit, interested patients will provide written informed consent and the link to the baseline questionnaire to be completed via Qualtrics. Each participant will receive a $20 gift card after completing the questionnaires. Following enrollment, participants will be referred to MTS for assignment to a CHW.

The CHW will schedule an initial session (60 minutes) with participants, followed by 5 subsequent monthly sessions (virtual or telephone-based) scheduled for 30 to 60 minutes, for a maximum of 6 patient contact hours over 6 consecutive months. During each monthly session, the CHW will educate participants on SCD management (ie, preventive services, management of acute complications, and management of chronic complications). The CHW will use a subjective, objective, assessment, and plan (SOAP) format for reporting via Qualtrics. The SOAP form is a standardized documentation method used by health care providers to systematically record patient information, thereby enhancing communication about health care experiences [24]. By organizing patient encounters into 4 distinct sections, the SOAP note serves as a clear framework for evaluating patient data and outlining management strategies [24]. This report will allow the CHW to document observations from patient interactions.

After completion of the sixth and final session, the CHW will provide a link to the postintervention questionnaire to be completed via Qualtrics. The postintervention questionnaire contains a question of interest about participating in debriefing interviews. We will conduct semistructured debriefing interviews with patients (n=35 approximately) to determine the perceived feasibility and acceptability of the study procedures. A member of the research team will conduct the interviews using a semistructured interview guide. Interviews are expected to last 45 to 60 minutes, and compensation will be a US $25 gift card. All incentives will be distributed by the PI per the institutional review board–approved protocol for research involving human subjects.

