### Measures

#### Overview

Eligible patients will be referred to MTS for assignment to a CHW. At the initial session, participants will complete a baseline survey assessing patient satisfaction and self-report self-care behaviors. We will use a demographics questionnaire, the Medical Outcomes Study Patient Satisfaction Questionnaire [25], and the Jenerette Self-Care Assessment Tool [20] (refer to Multimedia Appendix 1 for details). The CHW will complete a SOAP report at each session, documenting observations of the participant’s condition and responses related to self-care behaviors. After each visit, the CHW will report the results to the PI. These sessions will allow the PI to assess study fidelity and address any challenges with implementation or potential participant dropout. It will also allow the research team to determine whether modifications to the program are needed to ensure participant retention. During the final CHW session, the participant will complete a postintervention survey on patient satisfaction and self-report self-care behaviors.

Patient satisfaction with medical care will be assessed using the Medical Outcomes Study’s Patient Satisfaction Questionnaire Short Form (PSQ-18) [25]. The PSQ-18 is an 18-item self-report instrument designed to evaluate patients’ satisfaction with health care services across multiple domains, including general satisfaction, technical quality, interpersonal manner, communication, financial aspects, time spent with providers, and accessibility and convenience. Items are rated on a 5-point Likert scale ranging from strongly disagree to strongly agree. Subscale scores are computed by averaging item responses, with higher scores indicating greater satisfaction with care. The PSQ-18 has demonstrated good reliability and validity across diverse patient populations and is widely used in health services research [25].

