### Data Analysis

SPSS (version 25; IBM Corp) will be used to analyze quantitative data collected from the survey instruments. Categorical data will be described using frequencies and percentages. Continuous measures will be described using means and SDs. Cronbach α will be used to calculate the internal consistency for the instruments [26]. To examine relationships between measures, *χ*^2^ tests will be used for categorical variables, paired *t* tests will be used to compare pre-post measures, and ordinary least squares multiple regression analyses will be conducted to examine associations between demographic variables and outcome measures. Missing data will be minimized using stop measures including using Qualtrics to prevent skipping questions and applying case deletion for surveys with missing entries that are important to answer the primary research question.

NVivo (version 15; Lumivero) will be used to analyze qualitative data collected through semistructured interviews. Data will be transcribed, deidentified, and coded for analysis [27]. To ensure rigor, we will work with another member of the research team associated with the parent grant to independently analyze the transcripts. Findings from the 2 independent analyses will be reviewed and refined until agreement is reached [28]. Findings will be reviewed for accuracy of data interpretation, themes generated, and conclusions drawn.

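### The post-intervention questionnaire is tied to the sixth CHW session, so reachable participants who stop earlier are never measured on the primary outcomes

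*Protocol article*

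**What the plan says.** All references are to the Protocol article.

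- **Outcomes and timing (Procedures and Data Collection).** "The primary outcomes for this study are patient satisfaction and self-care behaviors", and appointment keeping is named as one component of self-care. On timing: "These will be assessed using validated instruments at baseline and after intervention (following the 6-month CHW-integrated PCCC model"). No intermediate measurement with these instruments is described. The same section makes retention and intervention completion feasibility outcomes.
- **Release of the post questionnaire (Study Procedures).** "After completion of the sixth and final session, the CHW will provide a link to the postintervention questionnaire to be completed via Qualtrics". The question that asks about interest in a debriefing interview is inside this questionnaire.
- **Second statement of the release (Measures, Overview).** "During the final CHW session, the participant will complete a postintervention survey on patient satisfaction and self-report self-care behaviors".
- **Analysis (Data Analysis).** Paired *t* "tests will be used to compare pre-post measures". Missing data are limited by blocking skipped questions in Qualtrics and by "applying case deletion for surveys with missing entries that are important to answer the primary research question".
- **Attrition (Study Design, Setting, and Sample).** The target is 40. "This sample includes an expected 20% attrition rate", and the principal investigator may "enroll additional participants if an enrolled participant is lost to follow-up".

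**The concern.** Measurement is triggered by attendance and not by time since enrolment. A person who drops out of the sessions but would still answer a survey has no described way to receive one. The paired test needs both scores, so that person's baseline contributes nothing to the pre-post comparison either.

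This differs from ordinary attrition in three ways. Reaching the last scheduled session is close in kind to appointment keeping, which is part of a primary outcome. Enrolling replacements restores the number analysed but not the people who left, so the analysed group is refilled with others who reach session six. And the design has no comparison group in which similar selection could be seen.

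The second specific aim is to evaluate effectiveness on self-care and satisfaction, and the results are meant to inform later trials. A change that applies only to those who stayed could mislead that planning. Acceptability is affected too: early stoppers are not offered the interview-interest question, although they could best explain why the programme did not suit them.

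**Working it through.** **Step 1. Who can have a post score.** The two statements of the trigger differ in detail: one places the survey after the last session, the other during it. Both require the participant to reach that session. The CHW's SOAP reports are visit records and not the outcome instruments, so they do not fill the gap. The reporting of possible dropout to the principal investigator serves retention; it does not provide for surveying people who leave.

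**Step 2. The plan's own numbers.** With 40 enrolled and 20% attrition:

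- without a post score: 40 × 0.20 = 8
- pairs analysed: 40 × 0.80 = 32

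For a two-sided paired *t* test at α = 0.05 and 80% power (noncentral *t*), the detectable standardised change is 0.51 with 32 pairs and 0.45 with 40. The article's stated range of 0.4 to 0.6, read as standardised changes, would need 52 pairs (52 / 0.8 = 65 enrolled) at the lower end and 24 pairs (24 / 0.8 = 30 enrolled) at the upper end. A target of 40 therefore does not reproduce across that range. That is a separate matter, and the present point does not depend on it.

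**Step 3. What selection could do.** Let *a* be the unmeasured fraction, Δ₁ the mean change in those who reach session six and Δ₀ the mean change in the rest:

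Δ(all) = (1 − *a*)Δ₁ + *a*Δ₀

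The plan's estimate targets Δ₁, so it differs from Δ(all) by *a*(Δ₁ − Δ₀). The 20% is from the article. Δ₁ = 0.50 SD and every value of Δ₀ are assumptions.

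| Δ₀ (assumed) | Calculation | Δ(all) |
|---|---|---|
| half of Δ₁ (0.25) | 0.8 × 0.50 + 0.2 × 0.25 | 0.45 |
| no change (0) | 0.8 × 0.50 + 0.2 × 0 | 0.40 |
| worse by 0.2 | 0.8 × 0.50 + 0.2 × (−0.2) | 0.36 |

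With Δ₁ = 0.71, the effect size the article cites from earlier self-care studies, the three results are 0.64, 0.57 and 0.53. With Δ₁ = 0.50 and no change in the rest, Δ(all) is 0.45 at *a* = 10%, 0.35 at 30% and 0.30 at 40%. If Δ₀ equals Δ₁ there is no distortion, and if Δ₀ exceeds Δ₁ the plan's estimate is too low.

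**Step 4. How much a survey at a fixed time could recover.** Suppose a fraction *f* of the unmeasured 20% would answer, and that Δ₀ = 0 in both responders and non-responders. The mean among those with follow-up is (0.8 × 0.50) / (0.8 + 0.2*f*):

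- *f* = 0: 0.40 / 0.80 = 0.50
- *f* = 0.5: 0.40 / 0.90 = 0.44
- *f* = 1: 0.40 / 1.00 = 0.40

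The article gives no basis for *f*.

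**The case against.** Several stronger readings are tempting, and the article does not support them.

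- **Only fully adherent participants are measured.** A reader might infer this, but the condition is reaching session six. The text does not say that someone who missed an earlier session is excluded, or that a missed session cannot be rescheduled.
- **Every incomplete survey is deleted.** Deletion covers entries important to the primary question, and Qualtrics blocks skipped items. The main loss comes from questionnaires never sent.
- **The result is biased upward by a quarter.** That figure (0.50 / 0.40 = 1.25) is one row of the table. A paired test removes stable differences between people, so bias needs a difference in change. Participants who start with good self-care may have less room to improve.
- **All 8 could be measured.** The 20% includes people who could not be contacted on any schedule. Power at a standardised change of 0.5 is 78% with 32 pairs and 87% with 40, but the second figure assumes no loss and is an upper bound. The sample size already allows for 20% attrition and replacement is permitted, so lost power is not the main harm.

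It is also fair to say that this is a single-arm study producing preliminary data, that retention and completion will be reported so readers can judge how selected the group is, and that analysis sets and sensitivity analyses are commonly left to a full protocol or analysis plan that is not shown.

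These arguments lower the severity but do not remove the point. The article states the release rule twice, so this is a stated procedure and not an omitted detail. Reporting completion rates does not supply the missing scores.

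**Conclusion.** The point holds in limited form. As written, the pre-post change in the primary outcomes describes participants who reach session six. Those who stop earlier but remain reachable are left unmeasured by procedure. The estimate may be selected, plausibly in favour of the intervention, because appointment keeping belongs to the self-care outcome and lost participants are replaced. Neither the direction nor the size is established.

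The range of 0.36 to 0.45 SD against 0.50 SD is hypothetical. It rests on 20% unmeasured and on assumed changes in people the plan does not observe, and only part of any gap could be closed.

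This is a cheap improvement that should be made. It does not invalidate a feasibility study. It is best made soon: 16 participants were enrolled as of March 2026, and scores not collected at the time cannot be recovered by later analysis.

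**What to change.** 1. Have the research team send the post-intervention Qualtrics link, including the interview-interest question, to every enrolled participant 6 months after baseline, whatever number of sessions was attended.
2. Make the main pre-post analysis all enrolled participants with follow-up, and report those who reached session six as a secondary analysis.
3. Add a simple sensitivity analysis that assigns no change to those still missing. With 20% missing it multiplies the observed mean change by 0.8. A repeated-measures model with two time points would add little for baseline-only participants; the gain comes from collecting the data.
4. Reconcile Study Procedures with the Overview under Measures on whether the survey is done during or after the final session.

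**Cost:** a few extra survey links, reminders and any survey incentive, plus a short change to the procedure and analysis wording. The estimated change may come out smaller.

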### Ethical Considerations

This protocol will be conducted in accordance with the Declaration of Helsinki. Ethics approval has been granted on an expedited basis by the institutional review board of Georgia Southern University (H21406) for surveys and interviews conducted with human subjects. Informed consent will be obtained from all participants, who will then receive a link to the baseline questionnaire to be completed via Qualtrics XM (Silver Lake and CPP Investments). Each participant will receive a US $20 gift card after completing the questionnaire.

Health Insurance Portability and Accountability Act (HIPAA)–protected information will not be discussed during calls. Information collected during calls will be stored on a cloud server that is only accessible to the research team. To protect the confidentiality of participants, each of them will be assigned a unique participant code.

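### Follow-up self-reports of both primary outcomes are collected through or with the CHW, and the protocol contradicts itself on whether baseline is collected the same way

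*Protocol article*

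**What the plan says.** Two sections of the protocol article describe how the primary outcomes are collected, and they differ.

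- **Study Procedures, baseline:** "During the visit, interested patients will provide written informed consent and the link to the baseline questionnaire to be completed via Qualtrics". Read literally, patients supply the link. Ethical Considerations makes the meaning clear: participants consent, "who will then receive a link to the baseline questionnaire to be completed via Qualtrics XM". The CHW enters only later: "Following enrollment, participants will be referred to MTS for assignment to a CHW".
- **Study Procedures, follow-up:** once the sixth session is over, "the CHW will provide a link to the postintervention questionnaire to be completed via Qualtrics".
- **Measures, Overview, baseline:** after describing referral for CHW assignment, "At the initial session, participants will complete a baseline survey assessing patient satisfaction and self-report self-care behaviors".
- **Measures, Overview, follow-up:** "During the final CHW session, the participant will complete a postintervention survey on patient satisfaction and self-report self-care behaviors".

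Procedures and Data Collection names patient satisfaction and self-care behaviors as the primary outcomes. Both are self-reported, by the PSQ-18 and an SCD self-care tool. The design is a single-group pre-post comparison, and under Data Analysis "paired *t* tests will be used to compare pre-post measures".

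**The concern.** A pre-post change can be read as an effect of the intervention only if the measurement itself stays the same. Here the participant has spent six monthly sessions being taught self-care by the CHW, who also records the participant's responses about self-care in each session report. The participant is then asked to self-rate self-care, and satisfaction with the care that the CHW has joined, by means of that same CHW. Some participants may answer more favorably than they otherwise would.

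If Study Procedures governs, the person behind the request also differs between the two time points: clinic enrollment at baseline, the CHW at follow-up. There is no comparison group in which the same measurement effect would appear and cancel. Aim 2 is to evaluate effectiveness on exactly these two outcomes, and the results are meant to shape a later study. A shift caused by the way the answers were requested could therefore be carried forward as an effect of the model.

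**Working it through.** **Step 1. Set the two accounts side by side.**

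| | Study Procedures (with Ethical Considerations) | Measures, Overview |
|---|---|---|
| Baseline | Link given with consent at the clinic visit, before CHW assignment | Completed at the initial session, after referral for CHW assignment |
| Follow-up | Link supplied by the CHW after session six | Completed during the final CHW session |
| Does the route change? | Yes | No |
| Is the CHW involved at follow-up? | Yes | Yes |
| Does the CHW relationship differ between time points? | Yes: none at baseline, six months at follow-up | Yes: first meeting at baseline, six months at follow-up |

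The last two rows give the same answer on both accounts. The change of route appears on one only.

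**Step 2. Ask what the design can separate.** Write the observed mean change as the true change plus a measurement shift. The paired t test estimates the sum. Without a comparator the two parts cannot be told apart.

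**Step 3. Size, under an assumed shift.** The protocol states no figure for such an effect, so there is none to reproduce.

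Inputs:
- target n = 40 and 20% attrition (Study Design, Setting, and Sample), giving 40 × (1 − 0.20) = 32 pairs
- two-sided α = .05 (same section)
- true change = 0
- measurement shift δ = 0.1, 0.2 or 0.3 SD of the change score (assumed)

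The paired t statistic then follows a noncentral t distribution with n − 1 degrees of freedom and noncentrality δ√n. The chance of a significant result is the probability that |t| exceeds the two-sided 5% critical value.

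| δ (SD of change) | δ√32 | Significant, 32 pairs | δ√40 | Significant, 40 pairs |
|---|---|---|---|---|
| 0 | 0 | 5% | 0 | 5% |
| 0.1 | 0.57 | 8.5% | 0.63 | 9.5% |
| 0.2 | 1.13 | 19.5% | 1.26 | 23.5% |
| 0.3 | 1.70 | 37.6% | 1.90 | 45.7% |

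These rates apply to each outcome separately.

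**Step 4. If the shift runs the other way.** For satisfaction the baseline answer could be the inflated one (see the objection). A downward shift would hide benefit. With 32 pairs and a true gain of 0.5 SD of the change score, power is 78.2%. A downward shift of 0.2 SD leaves an apparent gain of 0.5 − 0.2 = 0.3 SD, and power falls to 37.6%.

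**The case against.** The strongest reply is that the change of route is not established. The Overview of Measures places both surveys in CHW sessions, so on that account the route is constant. The baseline accounts might even be combined, with the link given at the clinic and the form filled in at the first session. This stands: a reader of Study Procedures alone might infer that the collector definitely changes, and the article does not settle it. It does not remove the point, because on both accounts the follow-up survey passes through the CHW after six months of contact.

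Other objections also stand, wholly or in part:

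- **What is rated.** A reader might infer that participants are rating the CHW's own work. They are not. The PSQ-18 covers health care services in general, and the other tool covers the participant's own behavior. Satisfaction with the intervention and rapport with the CHW are covered in interviews, and a research team member conducts the patient interviews.
- **Direction.** A reader might infer that a courtesy effect is absent at baseline and favors the intervention on both outcomes. The documents do not support this. Clinic staff, who belong to the service being rated, offer the study at the clinic visit, so baseline satisfaction could carry courtesy pressure of its own.
- **The CHW's role.** The CHW supplies a link and the participant completes the form. Nothing says that the CHW administers it or sees the answers.
- **Existence and size.** The shifts of 0.1 to 0.3 SD are assumptions. The percentages show what such a shift would do, not that one occurs.
- **Other evidence.** The interviews ask about rapport and influence on self-care, and the results are to be triangulated. That may hint at a bias but cannot quantify it.
- **Limits of the remedy.** Social desirability after six months of coaching would not vanish if someone else sent the link. Changing the sender reduces the risk; it does not abolish it.

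**Conclusion.** Two things are firm. Study Procedures and the Overview of Measures contradict each other on when and through whom baseline is collected, and on whether the follow-up survey falls during or after the last session. And on either account, the follow-up self-reports of both primary outcomes are obtained through or with the intervention deliverer, in a design that cannot separate a measurement effect from real change.

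The bias itself is a plausible risk, not a demonstrated one. For self-care the likelier direction is favorable; for satisfaction it is open. If the shift were 0.1 to 0.3 SD of the change score, the false-positive rate per outcome would be about 8.5% to 38% with 32 pairs, instead of 5%. That range rests on the assumed shift, zero true change and 20% attrition from 40. The study's stated objective is feasibility and acceptability, so this is a cheap improvement to the effectiveness aim and not a flaw that defeats the study.

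**What to change.** 1. Reconcile Study Procedures with the Overview of Measures, so that one time and one route are stated for each survey.
2. Have the research team send both Qualtrics links directly to the participant, keyed to the existing participant code, by the same route and with the same text, stating that neither the CHW nor clinic staff will see the answers. The CHW's part is at most to remind participants that a survey is due.
3. For those already enrolled (16 by March 2026), record which route was used at each time point, and report it with the results.

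The cost is a Qualtrics distribution setting and a few sentences of procedure. The research team already conducts the patient interviews and the principal investigator distributes the incentives, so direct contact with participants exists. The downsides are a few more reminders than when the CHW prompts in person, and a possible mix of routes among early enrollees, which the record in step 3 makes visible.
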